Despite the significant anti-hypertensive effects demonstrated in the FlaxPAD trial, the results contained some important limitations. Firstly, participants of the FlaxPAD trial were already on anti-hypertensive medication yet still exhibited poorly controlled blood pressure [8]. Therefore it is not possible to conclude if flaxseed can reduce blood pressure as a monotherapy or if it is only effective in conjunction with anti-hypertensive medication. Secondly, it remained unclear if flaxseed could effectively reduce blood pressure in hypertensive patients without coexisting peripheral arterial disease. Therefore, despite evidence showing the potential of flaxseed as a potent cardioprotective functional food, the efficacy of flaxseed as an independent treatment to reduce blood pressure in newly diagnosed patients with primary hypertension has yet to be investigated.

The hypothesis to be tested in the present study is: dietary flaxseed will reduce blood pressure in patients with newly diagnosed hypertension and will reduce the need for anti-hypertensive medication. In order to test these hypotheses, a phase II, randomized, double-blinded, controlled clinical trial called HYPERFlax has been designed. The acronym for the HYPERFlax trial stands for the anti-HYPERtensive effects of dietary Flaxseed. Parameters such as blood pressure, plasma and urine metabolomics, plasma lipid profiling, and plasma vascular tone regulators will be analyzed to assess the efficacy and mechanisms of action of dietary flaxseed in hypertension management.

The aims of the HYPERFlax trial are to:

1. determine if consuming 30 g of milled flaxseed daily can effectively reduce blood pressure over six months in newly diagnosed stage 1 primary hypertensive participants;

2. determine if dietary flaxseed is efficacious as a monotherapy;

3. determine if flaxseed can reduce the need for anti-hypertensive medication; and

4. identify the mechanisms of action responsible for the potential anti-hypertensive effects of flaxseed.

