### Settings and participants

The trial will take place at the Health Sciences Centre Hospital and St Boniface Hospital in Winnipeg (Manitoba, Canada). The aim is to enroll 100 participants. Based on the previous FlaxPAD trial [8] the expected attrition rate is 20%, which still allows for a power of 0.80 to detect differences between groups and across time, out of an effect size of 0.7 (SD) at an α level of 0.05. Participants will be recruited through doctor referral or in response to public advertisements and public screening booths. The inclusion and exclusion criteria below fit the criteria of individuals who are not recommended to be administered anti-hypertensive medication immediately according to the Canadian Hypertension Education Program Guidelines [9]. These individuals do not have a systolic or diastolic blood pressure of more than 160/100 mmHg and do not have diabetes or macrovascular target organ damage. The exclusion criteria, therefore, allow a period of time for lifestyle intervention, including new therapeutic strategies like dietary flaxseed, in low-risk hypertensive individuals.

Inclusion criteria includes:

1. stage 1 essential hypertension (average automated systolic blood pressure of 135 to 160 mmHg or diastolic blood pressure of 85 to 100 mmHg) [9];

2. Newly diagnosed; defined as being clinically diagnosed within the last six months. This includes being diagnosed at the screening examination;

3. Male or female;

4. Untreated by medications for hypertension;

5. 18 to 85-years-old and able to provide informed consent;

6. Females who are not pregnant and not planning on becoming pregnant during the course of the trial. A pregnancy test will not be administered for the trial;

7. Subjects who are receiving anti-platelet therapy must be on a stable dose for three months prior to the study;

8. Subjects who are receiving lipid-lowering drugs must be on a stable dose for three months prior to the study;

9. Subjects must have access to freezer space in their residence to hold up to one month of the frozen food products associated with this study.

Exclusion criteria includes:

1. Patients with ischemic pain at rest in limbs, ulceration, or gangrene.

2. Patient has undergone percutaneous coronary angioplasty, or has had coronary bypass within the last six months.

3. Known secondary hypertension of any etiology.

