### Participant assessments

#### **
*Averaged automated blood pressure*
**

The primary outcome measure is blood pressure. Blood pressure will be measured at a total of five visits: screening, baseline, two, four, and six months. A BPTru machine will be utilized to measure blood pressure six times within 10 to 15 minutes. The first reading will be discarded and the remaining five will be averaged. This measurement will take place in a quiet room while the participant is in a seated position and arm rested on an arm rest at heart level. A blood pressure reading with a sphygmomanometer and stethoscope will also be performed to ensure the congruency between this measurement and the automated measurement.

#### **
*Need for anti-hypertensive medication*
**

One of the secondary outcome measures is the need for anti-hypertensive medication. In the first two months of the trial the participants will not be prescribed anti-hypertensive medication as this is the lifestyle intervention period. A meta-analysis published in 2008 concluded the administration of a placebo to patients with hypertension for four to eight weeks provided no objective reason against safety [12]. At two, four, and six months the participants will have a blood pressure follow-up. The participants will be assessed for the need for anti-hypertensive medication. If deemed necessary, they will be prescribed anti-hypertensive medication according to the Canadian Hypertension Education Program guidelines. If prescribed anti-hypertensive medication, the type and dose of anti-hypertensive medication will be recorded. If a follow-up visit is required sooner than the two-month interval, the patient will be asked to return to the clinic for more visits as standard of care.

#### **
*Anthropometrics and questionnaires*
**

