All data will be stored without identifiable participant information in a password protected electronic document or locked cabinet. The final trial data set will be accessible only to researchers involved in the trial and any medical review board that requires access for safety purposes. In the likelihood of an unbalanced data set, absolute values will be analyzed with a mixed two-way repeated measures model with group and time as the between and within factor, respectively. A *post-hoc* comparison of the least squared means with a Tukey’s adjustment will be utilized to determine where the specific differences lie. Absolute change will also be calculated only for participants who provide clinical information and samples at all time points. Absolute change can be analyzed with one way analysis of variance (ANOVA) and the Kruskal-Wallis test, or multiple *t*-tests and the Mann Whitney U test with a false discovery rate correction. Multiple regression may be used to determine the influence of flaxseed on blood pressure while including factors such as age, BMI, gender, diet, or physical activity. Correlations will be utilized to determine relationships between biochemical markers and blood pressure. Subgroup analyses may also be performed, for example, the dichotomization of change in biochemical markers and observing subsequent change in blood pressure. All statistical tests will be set at a significance level of 0.05. Data will be published in peer-reviewed journals and discussed in public forums such as radio and television broadcasts.

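### Anti-hypertensive drugs may start from month 2, but the stated model uses group and time only, so it does not isolate the six-month monotherapy effect that aim 2 asks for

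*Protocol article*

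**What the plan says.** All from the protocol article.

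- **Aims (Background).** Aim 1 concerns the reduction in blood pressure over six months. Aim 2 is to "determine if dietary flaxseed is efficacious as a monotherapy". Aim 3 concerns the need for anti-hypertensive medication. The Background gives concurrent medication as a reason why the earlier flaxseed trial could not settle the monotherapy question. The Discussion repeats that flaxseed is to be evaluated as a monotherapy.
- **Drug start (Participant assessments, Need for anti-hypertensive medication).** No drugs are prescribed in the first two months. Need is assessed at months 2, 4 and 6: "If deemed necessary, they will be prescribed anti-hypertensive medication according to the Canadian Hypertension Education Program guidelines". Type and dose are recorded, extra clinic visits are possible, and need for medication is a secondary outcome.
- **Analysis (Statistical analysis).** Blood pressure is the primary outcome, and "absolute values will be analyzed with a mixed two-way repeated measures model with group and time as the between and within factor, respectively". The optional regression gives example covariates, none of them medication. The change analysis is restricted by completeness of data, not by drug status.

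**The concern.** Blood pressure decides who starts drugs, and drugs then lower blood pressure. A month-4 or month-6 reading on drug counts in the stated model exactly as a drug-free reading does. If flaxseed works, more control participants should need drugs, which is what the hypothesis predicts. Their later readings then fall because of the drug, and the difference between groups narrows. From month 2 the design lets back in the factor that the trial was set up to exclude, and the analysis described has nothing to separate it out.

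What is at stake is a missed or understated monotherapy effect at months 4 and 6, not a false positive.

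**Working it through.** **1. The plan's own figure.** Settings and participants gives 100 enrolled, 20% attrition (so 40 per arm), an effect of 0.7 SD and alpha 0.05, "which still allows for a power of 0.80 to detect differences between groups and across time". Taking a two-sided test of two means by the normal approximation:

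power = Φ(0.7 × √(40/2) − 1.960) = Φ(3.130 − 1.960) = Φ(1.170) = 0.88 (t-test 0.87).

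The stated 0.80 is therefore conservative for this simple contrast. That is a separate matter, but it sets the margin. Power of 0.80 needs (1.960 + 0.842)/√20 = 0.63 SD, so about 0.07 SD can be lost before power drops below the stated level.

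**2. Simple attenuation formula.** Let pC and pF be the shares on drug by month 6 in control and flaxseed, and d the drug effect in SD, equal in both arms. Then

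observed month-6 effect = 0.7 − (pC − pF) × d.

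The documents give none of pC, pF or d; all are assumed. Example with 30% and 10% and d = 1.0: 0.7 − 0.20 × 1.0 = 0.50 SD, power Φ(0.50 × √20 − 1.960) = Φ(0.276) = 0.61.

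| pC / pF | d = 0.5: effect (power) | d = 1.0: effect (power) |
|---|---|---|
| 20% / 10% | 0.65 (0.83) | 0.60 (0.77) |
| 30% / 10% | 0.60 (0.77) | 0.50 (0.61) |
| 50% / 20% | 0.55 (0.69) | 0.40 (0.43) |
| 30% / 30% | 0.70 (0.88) | 0.70 (0.88) |
| 10% / 20% | 0.75 (0.92) | 0.80 (0.95) |

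Equal starts give no attenuation, and more starts on flaxseed push the difference the other way. The formula holds the SD fixed. Drug use in fact narrows the spread, which gives back a little power.

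**3. Drug start driven by pressure.** This simulation lets the readings decide who starts. All inputs are assumed: 40 per arm, SD 10 mmHg (so 0.7 SD is 7 mmHg), correlation 0.6 between visits, baseline mean 145 mmHg, a 3 mmHg fall in both arms, the full effect of −7 mmHg from month 2, a start at month 2 or 4 when systolic pressure exceeds a trigger, and a drug effect of −5 or −10 mmHg. The triggers are sensitivity values, not proposed rules. With complete data the model's month-6 contrast is the plain difference in means.

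| Trigger (mmHg) | Starts, control / flaxseed | Month-6 difference, drug −5 / −10 | Power, drug −5 / −10 |
|---|---|---|---|
| 140 | 72% / 44% | −5.6 / −4.1 | 0.78 / 0.57 |
| 145 | 52% / 24% | −5.6 / −4.2 | 0.79 / 0.58 |
| 150 | 32% / 11% | −6.0 / −5.0 | 0.82 / 0.70 |
| 160 | 6% / 1% | −6.7 / −6.5 | 0.87 / 0.85 |

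Power here is by the normal approximation; simulated trials of 40 per arm put the lowest entry at about 0.55. If only half the effect is present at month 2, triggers of 140 to 150 give about −5.0 to −6.3 mmHg and power of roughly 0.73 to 0.86. With a true effect of zero the month-6 contrast stays at about zero. The month-2 contrast is untouched throughout.

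**4. Two possible repairs, triggers 140 to 150.** Keeping only participants who never started drugs gives −3.7 to −5.1 mmHg, so it does not recover −7. Setting post-drug readings to missing in a likelihood analysis that keeps baseline and all earlier readings gives −7.0 to −7.2 mmHg. Its standard error rises from about 2.0 to between 2.1 and 3.1 mmHg. The recovery is expected, because the simulated drug starts depend only on observed readings.

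**The case against.** The strongest reply has four parts.

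- **Silence.** The article condenses a fuller protocol, and an unseen analysis plan may handle readings on drug. Drug type and dose are recorded, and the regression's covariate list is open. This stands as a caution. But the article does fix the model and its factors, and that model does not match aim 2.
- **Direction.** A reader might infer that the flaxseed effect is simply biased toward zero. The documents do not support that as a fact. It needs a true effect and more drug starts in control. For a treatment-policy question, the effect whatever drugs are added, the smaller difference is the target and not a bias. Aim 1 can be read that way.
- **Answerability.** A reader might also infer that aim 2 cannot be answered, or that a null result could not be told from rescue of controls. That goes too far. Month 2 is drug-free by rule in both arms and is a visit in the model, and an excess of drug starts in control would show in the secondary outcome. Month 2 is only partial support, though: products are introduced gradually over the first month (Reporting and evaluation of serious adverse events), and month 2 does not give a six-month effect.
- **Size.** Every input to the dilution is assumed. With a 160 mmHg trigger it almost disappears. The simulation is systolic only, although entry is by systolic or diastolic pressure. This stands.

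**Conclusion.** The point holds in a limited form: the stated model, followed as written, mixes drug effects into the month-4 and month-6 contrasts and so does not isolate the six-month monotherapy effect of aim 2. If flaxseed works and more control participants start drugs, those contrasts understate that effect.

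Under the assumed inputs a true 7 mmHg difference at month 6 appears as about 4.1 to 6.7 mmHg, and power goes from about 0.87 to between 0.55 and 0.87. Where in that range the trial would fall depends on the drug-start trigger and the drug effect, neither of which the article gives. The concern does not extend to the month-2 contrast, to false-positive risk, or to aim 1 if that is meant as a treatment-policy question.

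**What to change.** Before unblinding, add to the analysis:

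1. **For aim 2, a drug-free estimand.** Set readings after a participant's first anti-hypertensive prescription to missing. Fit the likelihood-based mixed model to all earlier readings, including baseline and any unscheduled-visit pressures that prompted drug start. A reading taken before a prescription at the same visit is kept.
2. **The assumption.** State that this relies on missing-at-random, that is, on drug start being explained by recorded pressures. Clinical judgement or unrecorded interim readings would weaken it. Present the drug-free month-2 contrast as support.
3. **No simple exclusion** of medicated participants.
4. **The all-readings (treatment-policy) analysis alongside**, with a statement of which of the two answers aim 1. That choice is a trade-off for the sponsor to make.

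Need for medication is already a secondary outcome; showing drug starts by arm next to both analyses lets a reader interpret any gap between them.

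The cost is mainly analysis wording. Drug type and dose are already recorded; the date of first prescription and any unscheduled pressures must be captured too. The price is a wider standard error at months 4 and 6 and reliance on missing-at-random. Nothing changes in when drugs are given.

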### Randomization and interventions

Upon acceptance into the trial all participants will be provided information on lifestyle management of hypertension. These strategies include the dietary approaches to stop hypertension, limiting alcohol and salt intake, limiting or stopping cigarette smoking, increasing physical activity, and losing weight if the individual is overweight or obese. However, it is not mandatory to adopt these lifestyle changes to be eligible for the trial.

Immediately after the baseline assessments, subjects will be randomized to one of two possible groups by a non-restricted computer-generated randomization schedule. The allocation ratio will be 1:1. The study coordinator will enroll the participants and the individual in charge of food delivery will be in charge of participant allocation. The allocation order will be in sequential, opaque, sealed envelopes. At this point all those involved in the study will be blinded to the group allocation excluding the individual responsible for food delivery.

The participants will be provided either the control or flaxseed-containing food products such as muffins, bagels, snack bars, and milled seeds to consume once a day for six months. A variety of flavors will be provided to assure the participants do not tire of the foods. In addition, participants will be encouraged to remain in the study and be adherent by describing to them the importance of their contribution to identifying new treatment strategies for hypertension. The control food products will contain a combination of wheat, pecans, and/or mixed dietary oils to replace the flaxseed. This combination of ingredients for the control food product will and has allowed for the best concealment and ability for a blinded trial. The formulation and flavor profiling of the flaxseed food products has been previously published [10,11].

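### The one firmly specified blood pressure model does not adjust for baseline blood pressure, which gives up precision the trial has already paid for

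*Protocol article*

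**What the plan says.** All references are to the protocol article. Under Participant assessments, the plan states "The primary outcome measure is blood pressure" and "Blood pressure will be measured at a total of five visits: screening, baseline, two, four, and six months".

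The Statistical analysis subsection then gives four routes to a result:

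- **The model.** With an unbalanced data set in prospect, "absolute values will be analyzed with a mixed two-way repeated measures model with group and time as the between and within factor, respectively". Attrition of 20% is expected (Settings and participants), so that condition will almost certainly be met.
- **The contrast.** A post-hoc "comparison of the least squared means with a Tukey’s adjustment will be utilized to determine where the specific differences lie".
- **Change scores.** "Absolute change will also be calculated only for participants who provide clinical information and samples at all time points". These may be compared by parametric or rank tests.
- **Regression.** It is optional, "while including factors such as age, BMI, gender, diet, or physical activity". Baseline blood pressure is not among the examples.

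Under Randomization and interventions, allocation uses a "non-restricted computer-generated randomization schedule", and "The allocation ratio will be 1:1". No stratification by starting pressure is described.

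**The concern.** Blood pressure at entry predicts blood pressure later. A comparison of group means that ignores it leaves explainable between-person variation in the error term. It also leaves part of any chance difference in starting pressure inside the treatment contrast. Unrestricted, unstratified allocation of about 100 people does nothing in the design to limit such a difference.

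The model does not say which visits form the levels of time. The natural reading is that baseline is one of them, because it is one of the scheduled measurements. In that case a least squares mean comparison at six months still makes no correction for where each group started. If instead only the follow-up visits are modelled, this model does not use baseline at all. Either way, the firmly stated comparison is unadjusted.

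What is at stake is the width of the confidence interval for the treatment effect and how far a single trial's result depends on the luck of the draw at baseline.

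**Working it through.** **Inputs from the article.** 100 enrolled, 20% attrition, 1:1 allocation, target effect 0.7 SD, α 0.05. This gives 100 × 0.8 / 2 = 40 per arm at the end.

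**Assumptions.** Two-sided testing, because sidedness is not stated. Equal variances at each visit, set to 1. A baseline/follow-up correlation ρ of 0.3 to 0.6. The article gives no ρ, and the eligibility window for entry pressure may lower it.

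**1. The plan's own figure.** The article states power 0.80. A two-sample t-test with 40 per arm at 0.7 SD has noncentrality 0.7 × √(40/2) = 3.13 on 78 degrees of freedom, so power is 0.871 (0.879 by the normal approximation). The stated 0.80 is not reproduced; it corresponds to about 33 per arm. The difference is on the conservative side and does not affect this point. The starting value below is 0.871.

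**2. Variance of the group difference at one visit, relative to no adjustment.** Unadjusted: 1. Change from baseline: 2(1 − ρ). Baseline as covariate: 1 − ρ². Power uses the noncentral t with effect 0.7 divided by the square root of the relative variance.

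| ρ | Change: variance | Change: power | Covariate: variance | Covariate: power |
|---|---|---|---|---|
| 0.3 | 1.40 | 0.74 | 0.91 | 0.900 |
| 0.4 | 1.20 | 0.81 | 0.84 | 0.921 |
| 0.5 | 1.00 | 0.87 | 0.75 | 0.946 |
| 0.6 | 0.80 | 0.93 | 0.64 | 0.972 |

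Covariate adjustment therefore removes 9% to 36% of the variance. It also beats the change score at every ρ below 1, because 2(1 − ρ) − (1 − ρ²) = (1 − ρ)², which is positive. Below ρ = 0.5 the change score is noisier than the raw follow-up value. These change-score powers also use 40 per arm; the planned analysis may have fewer, since it requires complete clinical data and samples.

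**3. Chance imbalance.** The baseline difference between arms has standard deviation √(2/40) = 0.224 SD. The part expected to carry into the unadjusted follow-up contrast is ρ times the difference: 0.3 × 0.224 = 0.067 SD to 0.6 × 0.224 = 0.134 SD. Relative to the 0.7 SD target that is 10% to 19%. The change score errs the other way, by (ρ − 1) times the difference: −0.157 to −0.089 SD.

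**4. A conditional case.** Suppose baseline is a level of time and the group main effect over four visits is the treatment test. An effect of 0.7 SD at each follow-up visit then averages to (0 + 0.7 + 0.7 + 0.7)/4 = 0.525 SD.

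**The case against.** Several things can fairly be said for the plan.

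- **Baseline is not ignored throughout.** A reader might infer that it serves only as a level of time. The article does not support that, because the change analysis uses each participant's starting pressure. That analysis is additional, restricted to complete cases and less efficient, so it softens the point without answering it.
- **The comparison is not biased.** A reader might infer that any baseline difference passes whole into the six-month result, or that the type I error rate is inflated. Neither follows. Only the ρ-scaled part is expected to carry forward, and chance imbalance is already reflected in the unadjusted standard error.
- **The main-effect dilution is hypothetical.** The article does not list the levels of time and never names the group main effect as the treatment test; it points to least squares means. A group-by-time contrast, if fitted with baseline as a level, would compare changes from baseline. It would remove the raw imbalance, but with the change score's precision and its overcorrection.
- **Power already looks sufficient.** At one visit 0.871 exceeds the stated 0.80, and at ρ = 0.3 the gain is only to 0.900. This stands for an uncorrected test. The planned comparison carries a Tukey adjustment over a family that is not stated. If it covered all eight group-by-visit cells, the critical value would be about 3.06 and unadjusted power about 0.53, against about 0.59 to 0.80 with baseline adjustment. The spare power may therefore not exist.
- **A full protocol or SAP may add the covariate.** It may, and the article does not rule this out. But the article states a specific model, and the point is that a better one is available for the same data.

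**Conclusion.** The point holds as one of efficiency and robustness, not validity. No blood pressure analysis in the article names baseline pressure as a covariate. The change-score alternative is less precise at any correlation below 1 and is limited to participants with complete data.

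The size of the loss depends on a correlation the article does not give. At the lower end of the range shown the gain from adjusting is modest; at the upper end it is equivalent to removing over a third of the variance. The power figures are for a single visit at an uncorrected two-sided 0.05 with 40 per arm, so they show the relative gain and are not the power of the planned Tukey-adjusted test. The dilution to 0.525 SD applies only under two conditions that the article does not state, and should not be reported as a feature of the plan.

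The article does not label the mixed model as primary, but it is the first-named and only firmly specified analysis of the primary outcome. The change should be made, because it costs nothing.

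**What to change.** Specify a mixed model with blood pressure at two, four and six months as the outcomes. The terms should be group, visit and group-by-visit, with baseline blood pressure and baseline-by-visit as covariates. An equivalent choice keeps baseline among the outcomes and constrains its mean to be equal in the two groups.

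State that the treatment effect is the group contrast at six months from this model, not the group main effect. Both forms use participants with some missing follow-up visits, so the complete-case change analysis can remain as supportive.

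The cost is a few lines of analysis wording, settled before unblinding. Baseline pressure is already scheduled for every participant, so no extra visits, measurements or participants are needed.

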The secondary outcome measures also include anthropometrics, food intake, and physical activity. At baseline, the participants will be asked to fast (9 to 12 hour overnight fast) for blood and urine collection. The blood and urine will be analyzed utilizing techniques including metabolomics and lipid profiling. Biological specimens will be coded with an anonymous patient code and locked in a -80°C freezer. Height, weight, and waist circumference will be measured and body mass index (BMI) will be calculated to assess if the intervention may cause any changes in weight or waist circumference. They will also be asked to fill out a 24-hour food recall form with the study coordinator using the multiple-pass method as established by the United States Department of Agriculture [13] and the standardized international physical activity questionnaire (short) [14]. These two surveys are used to assess the participants’ typical food intake and physical activity habits. These assessments will be repeated at two, four, and six months to assess any changes in diet or physical activity over time, as detailed in Figure 1.

#### **
*Biochemical analysis*
**

The secondary analysis will include the biochemical analysis of plasma or blood. Biochemical analysis also will be performed to determine potential anti-hypertensive mechanisms of action and adherence to intervention. Plasma samples from baseline, two, four, and six months will be analyzed for lipid profiles, metabolomics profile, and for any circulating plasma component that may influence blood pressure regulation. Plasma analysis of alpha-linolenic acid and enterolignans will act as adherence markers. Urine samples from baseline, two, four, and six months will also be analyzed for metabolomics profiling.

#### **
*Statistical analysis*
**

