### Reporting and evaluation of serious adverse events

No adverse effects are expected based upon published literature and our past experience with dietary flaxseed supplementation for one year [8]. Flaxseed has been granted Generally Recognized as Safe status by the Food and Drug Act 2009, USA and viewed as safe to consume for the general public [15]. Overall, toxicology and safety data in both human and animal trials have concluded flaxseed as safe to consume [16-23]. The food products provided to the participants will be prepared by companies that follow Good Manufacturing Practice of Health Canada. The perishable food products will be prepared, frozen, and stored frozen in a food warehouse. They will then be delivered frozen to the participants monthly.

Due to the ability of flaxseed to increase stool bulk and frequency of defecation, patients with a history of bowel obstruction, irritable bowel syndrome, or diverticular disease will be excluded. When large amounts of dietary fibre are consumed, gastrointestinal discomfort may occur. Results from our lab have indicated that the gastrointestinal discomfort and flatulence disappear within a few weeks once the participants have become accustomed to the fibre load. In addition, the gradual addition of flaxseed or wheat and wheat bran (control) throughout the first month allow the participants to become easily accustomed to the increase in fibre intake.

However, adverse events, as identified by the World Health Organization scale, will be followed up on if medically indicated, with relevant laboratory investigations under the direction of the study medical monitor. At this point, the medical board independent from the sponsor will be unblinded to the participant group allocation. Research staff will record the final outcome and the resolution date of the event wherever possible. If deemed necessary, the medical board will have the final say if the trial should be ended.

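### Change in blood pressure is also tested only in participants with complete clinical data and samples, a set selected after randomisation and not ranked below the mixed model

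*Protocol article*

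**What the plan says.** Under Participant assessments, the protocol article states: "The primary outcome measure is blood pressure". On timing it says: "Blood pressure will be measured at a total of five visits: screening, baseline, two, four, and six months". Blood and urine serve secondary, mechanistic and adherence purposes. Under Biochemical analysis, "Plasma samples from baseline, two, four, and six months will be analyzed for lipid profiles", and urine is collected at the same four visits.

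The Statistical analysis section describes two analyses in sequence:

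- **Absolute values.** "In the likelihood of an unbalanced data set, absolute values will be analyzed with a mixed two-way repeated measures model", with group and time as factors. No completeness condition is attached.
- **Absolute change.** "Absolute change will also be calculated only for participants who provide clinical information and samples at all time points". On testing, "Absolute change can be analyzed with one way analysis of variance (ANOVA) and the Kruskal-Wallis test, or multiple" *t*-tests and the Mann-Whitney test with a false discovery rate correction. All tests use the 0.05 level.

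The article does not say which of the two carries the conclusion on blood pressure, and it does not call the change analysis supportive. Under Settings and participants it says that "the expected attrition rate is 20" per cent.

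**The concern.** The change analysis is restricted by events after randomisation: attending every visit and giving every sample. The groups compared are then no longer the groups as randomised. If the people who leave differ in pressure response, and differ by arm, the contrast is distorted.

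The condition also joins two unrelated things. Blood pressure is the primary outcome and the samples are not. On the plain reading, a participant with a full set of pressure readings and one missed urine sample contributes nothing to the analysis of pressure change. There is no statistical reason for that exclusion.

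This matters because the first aim is whether pressure falls over six months, so a test of change in pressure speaks directly to the main question. With no ranking, a significant result in the complete set could be reported as efficacy evidence alongside, or in place of, the model that uses all readings.

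**Working it through.** **1. Inputs.** From the article: 100 enrolled, allocated 1:1, 20% attrition, effect 0.7 SD, alpha 0.05, stated power 0.80. Samples are taken at baseline and at two, four and six months. Randomisation follows the baseline assessments (Randomization and interventions), so only the three follow-up visits can produce losses after randomisation. Assumed: a two-sided test, since sidedness is not stated. The rates of missed readings or samples are also assumed, because the article gives none.

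**2. The plan's own figure.** After attrition, 100 × 0.8 = 80, or 40 per arm. Two-sample *t*-test, noncentrality = 0.7 × √(40/2) = 3.13, 78 degrees of freedom: power 0.87. This does not reproduce 0.80; the stated figure is conservative. With 33 per arm, power is 0.80. The complete set can therefore fall from 80 to about 66 before power reaches the stated level.

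**3. Power with missed samples.** Suppose each retained participant independently lacks a reading or sample at each of three follow-up visits with probability m. Complete per arm = 40 × (1 − m)³.

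| m (assumed) | Complete per arm | Retained participants dropped, of 80 | Power at 0.7 SD |
|---|---|---|---|
| 0% | 40 | 0 | 0.87 |
| 2% | 40 × 0.941 = 37.6 | 4.7 | 0.85 |
| 5% | 40 × 0.857 = 34.3 | 11.4 | 0.82 |
| 8% | 40 × 0.779 = 31.1 | 17.7 | 0.78 |

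**4. Selection.** On the plan's own attrition, about 20 of 100 randomised participants leave the change analysis before any missed sample is counted. To see what that can do, a simulation used four visits with autoregressive correlation 0.7. Dropout after month two or four followed a logistic rule on the pressure change so far, and 73% to 87% per arm completed. Units are the SD of a single reading, and negative values favour flaxseed. All of these settings are assumptions.

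| Dropout rule | True difference 0 | True difference −0.70 |
|---|---|---|
| Unrelated to pressure | 0.00 | −0.70 |
| Same pressure-related rule in both arms | 0.00 | −0.64 |
| Pressure-related in control arm only | +0.15 to +0.23 | −0.55 to −0.47 |
| Pressure-related in flaxseed arm only | −0.15 to −0.23 | −0.78 to −0.82 |

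A second run used equal correlation of 0.6 between all visits and let dropout depend on the current pressure level. It showed bias of about zero under every rule. Size and sign therefore depend on the dropout mechanism and the correlation structure, neither of which the article gives.

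**The case against.** The strongest reply is that the section already contains the safeguard. The mixed model comes first, is chosen because unbalanced data are expected, and carries no completeness condition. The change analysis is introduced as an addition. This stands, and it limits the point. A reader might infer that the trial's randomised comparison as a whole is reduced to completers, but the text does not support that. What remains is that nothing ranks the two analyses, and the change score has its own tests at 0.05.

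A reader might also infer that dropout will differ by arm.

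- The article does say "When large amounts of dietary fibre are consumed, gastrointestinal discomfort may occur". It adds that the discomfort settles after some weeks and that both the flaxseed and the wheat-based control are introduced gradually, so the fibre load is not confined to one arm.
- Participants whose pressure stays high may be prescribed medication, which is recorded. The article does not say that they leave.

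Differential dropout is therefore possible but not shown.

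Another tempting step is to assume that leavers on flaxseed gain nothing and scale the 0.7 SD effect down by the 20% attrition. No statement in the article supports zero benefit in leavers. A likelihood-based mixed model would not generally recover such a difference either, especially if they leave before giving follow-up readings.

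Finally, the sentence could mean that each change score needs only its own data at every visit, so that a missed sample would not remove a pressure change. That is a possible reading but not the plain one. The analysis would still be restricted to completers.

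**Conclusion.** The point holds as a should-fix matter about one stated analysis. Change in the primary outcome is tested in a set selected after randomisation, and on the plain wording that set can exclude complete pressure records because of a missing secondary sample.

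Selection is the larger harm. It is a risk that depends on dropout being related to pressure response and differing between arms. Under the assumed mechanisms its size ran from nil to about 0.23 SD, in either direction. Nothing in the article fixes where this trial would fall in that range.

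A reader might infer that the trial becomes underpowered. The figures do not bear that out: power falls from 0.87 to between 0.85 and 0.78 over the assumed miss rates, and drops below the stated 0.80 only once fewer than about 33 per arm are complete. Loss of usable readings is a reason to change the rule, but a secondary one.

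**What to change.** Amend the Statistical analysis section as follows:

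1. Name the mixed repeated-measures model as the main analysis of blood pressure, in all randomised participants, analysed as allocated, using every available pressure reading.
2. Estimate change from baseline as contrasts from that same model, not from a separate complete set.
3. State that inclusion in any blood pressure analysis does not depend on blood or urine samples.
4. Keep the all-visits set, if wanted, as a labelled supportive sensitivity analysis.

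The model protects against dropout that is explained by the recorded pressures. It does not protect against dropout driven by pressures never observed, and the text should say so. The cost is analysis wording only, with no extra visits, measurements or participants.
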